## **9.4 Statistical Analyses**

The SAP will be developed and finalised as early as possible after finalisation of the study protocol. Below is a description of planned statistical analyses. Further details are presented in the SAP.

### **9.4.1 General Considerations**

All statistical analyses will be performed by Parexel. All statistical analysis will be performed using the latest available version of SAS® (SAS Institute Inc., Cary, North Carolina, United States of America [USA]), version 9.2 or higher.

Continuous data will be summarised by treatment group using descriptive statistics (number, mean, median, standard deviation [SD], minimum, and maximum). Categorical data will be summarised by treatment group using frequency tables (frequency and percent).

Unless other way specified, baseline will be taken as the last available assessment prior to dosing on Day 1.

All statistical tests will be 2-sided and will be performed at the 5% level of significance, thus 95% confidence intervals (CIs) will be computed, unless otherwise stated.

A protocol deviation is defined as any change, divergence, or departure from the study design or procedures of a study protocol. Protocol deviations can lead to the exclusion of a subject from the PPS. Protocol deviations will be reviewed and classified at the Blinded Data Review Meeting (BDRM) prior to unblinding; the exclusion of subjects from PPS will be decided at BDRM.

Unless otherwise stated, missing data will not be imputed.

### **9.4.2 Primary Efficacy Endpoint**

For Part 1, refer to the safety analyses in Section 9.4.4.

For Part 2, the primary analysis for the primary endpoint (i.e., time to sustained recovery within the 28-day FU period) will be tested using the stratified (stratification factors used at randomisation) log-rank test in the FAS (if applicable) for the comparison of the 2 treatment arms. Kaplan-Meier curves will be presented, and median time to recovery and 95% CI will be calculated based on the Kaplan-Meier estimates. The Bayesian piecewise exponential model (Ibrahim et al 2001) will be used to calculate the time variant hazard ratios and 95% CI's. In this model, the stratification factors at the time of randomisation (if applicable) will be used as covariates. In these subjects with mild to moderate COVID-19 disease, no mortality or small mortality rate is

anticipated; in case of death events, a censoring time will be imputed to handle deaths similarly to cases of no recovery by Day 29.

Further details on the methodology applied for the statistical analysis will be described in the protocol and statistical analysis plan (SAP).

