| Efficacy                                                                                                                  |                        |                           |                                                                           |                |                |              |               |                |                |              |              |                |                 |
| Clinical status (8-point ordinal scale)                                                                                   |                        | X (pre-dose)              | Daily until hospital discharge and at each visit after hospital discharge |                |                |              |               |                |                |              |              |                |                 |
| Respiratory parameters b                                                                                       |                        | X (pre-dose)              | X                                                                         | X              | X              | X            | X             | X              | X              | X            | X            | X              | X               |
| COVID-19-Related Symptoms h                                                                                    |                        | X (pre-dose)              | X                                                                         | X              | X              | X            | X             | X              | X              | X            | X            | X              | X               |

|                                    | Screening a | Treatment period                  | Endpoint Assessment period |             |                |                |                |               |                | Extended FU    |                | Discharge | ED             |
|------------------------------------|------------------------|-----------------------------------|----------------------------|-------------|----------------|----------------|----------------|---------------|----------------|----------------|----------------|-----------|----------------|

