The IDMC will be asked to make a recommendation to progress to Part 2 (phase 2 design) of this study with the recommended dose based on the interim analysis of the Phase 1a study in 30 healthy subjects, supplemented with the available data from Part 1 of this study, even if not all Part 1 cohorts have reached the planned enrolment. This is due to recruitment challenges in Part 1 of this study resulting from low hospitalisation rate and reluctance of sites to participate and enrol patients in a phase I trial.

**Part 2 (Phase 2):** Part 2 consists of a double-blind, randomised, placebo-controlled Phase 2 study to evaluate the efficacy, safety, PK, and PD of XVR011 administered at the recommended dose level based on the IDMC review and recommendation. A total of 408 eligible subjects will be

randomised in a 2:1 ratio to receive either XVR011 (272 subjects) or placebo (136 subjects). Standard of care (SoC), according to local requirements will be allowed, except if listed in Table 6.5 Forbidden Concomitant Medications. Stratification will be done at randomisation for country and for fully vaccinated/prior SARS-CoV-2 infection. Subgroup analyses will include factors such as disease state, baseline serology, baseline viral load levels and duration of COVID-19 symptoms prior to study treatment.

For both Part 1 and Part 2 the study will consist of 3 periods: Screening (Day -1), Treatment period (Day 1), and Endpoint Assessment period (7 to 8 visits, Day 2 to Day 29); for Part 2 there will be an additional Follow-up period (2 visits, Day 60 and Day 90):

- **Screening (Day -1):** Subjects who are hospitalised and provide informed consent will undergo screening assessments as soon as possible after presentation with COVID-19 to evaluate their eligibility based on the inclusion and exclusion criteria. If eligible, the subject may be randomised (e.g for Part 1 this means IWRS treatment registration).
- **Treatment period (Day 1):** Within 12 hours of randomisation, a single intravenous infusion of study treatment will be started under medical supervision for the whole duration of the infusion and for two hours after the end of the infusion. This treatment will be administered in addition to SoC treatment.

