The proposed population is subjects, in whom the viral load is causing mild to moderate symptoms and who require supportive therapy such as hospitalised monitoring, treatment or supplemental oxygen but who are not in need of mechanical ventilation (i.e., level 4 or 5 of the 8-point ordinal scale). The aim of treatment with XVR011 is to neutralise the virus, to reduce the severity of the disease, and to prevent progression to severe complications such as ARDS or other major organ dysfunctions. Recovery is defined as reaching level 3 of the 8-point ordinal scale (i.e., subjects are hospitalised but no longer require supplemental oxygen or ongoing medical care for COVID-19) or less (subjects are no longer hospitalised for treatment of COVID-19). See also Section 2.1 and Section 2.2.

Study treatment will be administered in addition to SoC to limit the risk of disease progression for subjects randomised to placebo. For Part 2, concomitant use of remdesivir will be allowed as SoC, according to local guidelines.

Other small molecule antiviral agents such as molnupiravir and PF-07321332/ ritonavir may be continued at the discretion of the Investigator if they have been started prior to hospital admission for treatment of COVID-19 in accordance with their authorised use. However, they are not allowed if they are to be started once the subject is in hospital and in screening or already enrolled in the study.

Treatment with a SARS-CoV-2 neutralising monoclonal antibody for the current infection is not allowed with 4 weeks before and during the study, because of the similar mechanism of action and long half-life.

Stratification will be done at randomisation for country and for fully vaccinated/prior SARS-CoV-2 infection.

Subgroup analyses will include factors such as disease state, baseline serology, baseline viral load levels and duration of COVID-19 symptoms prior to study treatment.

Secondary endpoints to further evaluate efficacy include total duration of oxygen supplementation, proportion of subjects requiring mechanical ventilation or ICU transfer, subject-reported assessment of COVID-19-related symptoms following FDA Guidance for Industry (September 2020) and changes from baseline in viral load to evaluate antiviral activity.

Safety assessments will include standard adverse event reporting, physical examination, vital signs and ECGs, as well as the assessment of infusion related reactions (IRR) and hypersensitivity reaction.

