#### Type of Subject and Disease Characteristics

3. Has ongoing SARS-CoV-2 infection confirmed by positive RT-PCR test and/or positive antigen test  $\leq 72$  hours of randomisation\*. If the positive test result is older than 72 hours, a positive re-test (RT-PCR or antigen) during screening is required.
4. If dyspnoea and/or tachypnoea are present, an onset of at most 3 days prior to randomisation\* is allowed.
5. Requires medical care in hospital for COVID-19 (i.e., level 4 or 5 of the 8-point ordinal scale).

*\*For Part 1 randomisation means IWRS treatment registration.*

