## **8.1 Efficacy Assessments**

### **8.1.1 Clinical Status According to 8-point Ordinal Scale**

The clinical status will be assessed at the timepoints specified in the SoA (Table 1-1 for Part 1 and Table 1-2 for Part 2), using an 8-point ordinal scale (see Appendix 2), previously used in Study NCT04280705 (Beigel et al 2020).

Recovery will be defined as achieving a clinical status  $\leq 3$  on the 8-point ordinal scale. This will be considered 'sustained recovery' if the clinical status remains  $\leq 3$  for the subsequent 14 consecutive days. Time to sustained recovery will be defined as the time between treatment administration and the first occurrence of recovery which is subsequently shown to be sustained..

Deterioration in the clinical condition of the subject such that intensive care is required will be considered a treatment failure and the end of study visit should be performed.

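### The primary log-rank test and the piecewise model leave out baseline clinical status (level 4 or 5), so power is lost to the extent that level predicts recovery

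*Protocol*

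**What the plan says.** For Part 2, Section 9.4.2 states that the primary endpoint "will be tested using the stratified (stratification factors used at randomisation) log-rank test in the FAS". Section 4.1 names the factors: "Stratification will be done at randomisation for country and for fully vaccinated/prior SARS-CoV-2 infection". Section 6.3.2.1 repeats them. On the Bayesian piecewise exponential model that supplies the hazard ratios, Section 9.4.2 adds: "In this model, the stratification factors at the time of randomisation (if applicable) will be used as covariates".

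Section 5.1 admits a subject who "Requires medical care in hospital for COVID-19 (i.e., level 4 or 5 of the 8-point ordinal scale"). In Appendix 2, level 4 means in hospital without supplemental oxygen but still needing care, and level 5 means needing supplemental oxygen. Section 8.1.1 sets the event on the same scale: "Recovery will be defined as achieving a clinical status" of 3 or lower, which must then hold for 14 days. Table 1–2 lists "Clinical status (8-point ordinal scale") with a pre-dose entry on Day 1.

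Severity otherwise appears only among the subgroup factors in Sections 4.1 and 4.2: "Subgroup analyses will include factors such as disease state, baseline serology, baseline viral load levels and duration of COVID-19 symptoms prior to study treatment".

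**The concern.** Every subject starts at one of two levels of the scale on which the event is scored. A level 4 subject is already off oxygen and one step from recovery. A level 5 subject is two steps away and usually has to come off oxygen as well. A baseline value this close to the endpoint is a natural candidate for adjustment, more so than country or vaccination history, which have no comparably direct link to it.

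The protocol itself fixes the primary strata, so this is not a detail left open for the analysis plan. A subgroup analysis by disease state does nothing for the precision of the primary comparison. If level is prognostic, the primary test treats explainable variation as noise and has less power than the same data could give.

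**Working it through.** **Inputs from the protocol (Section 9.2, Table 9–1).** 408 subjects, 272:136; one-sided alpha 0.025; 80% power; 15% drop-out; 275 events. Not recovered at Days 5, 7 and 29: placebo 80%, 50%, 20%; XVR011 50%, 25%, 20%.

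**Inputs that are assumed.** The share at each level and the ratio of recovery rates are not given. Level 4 share: 50%, with 25% and 75% as variants. Level 4 to level 5 recovery hazard ratio: 1, 1.5, 2 or 3, so level 5 recovers at 1, 0.67, 0.5 or 0.33 times the level 4 rate.

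**Step 1: reproduce the plan.**
- Interval hazard ratios are ratios of log-survival differences: ln(0.50)/ln(0.80) = 3.11; ln(0.25/0.50)/ln(0.50/0.80) = 1.47; ln(0.20/0.25)/ln(0.20/0.50) = 0.24. All match Table 9–1.
- Events: 408 × 0.85 × 0.80 = 277, against 275 stated.
- Sample size, from the Lakatos-type expected log-rank statistic E(Z) at 408 × 0.85 = 346.8 evaluable subjects: N = 346.8 × ((1.960 + 0.842)/E(Z))² / 0.85. With E(Z) = 2.880, 2.820 and 2.753 (time steps of 0.01, 0.5 and 1 day), N = 386, 403 and 423, which brackets 408.
- Simulated power of the unstratified log-rank test with daily assessment: 80% to 82%.

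**Step 2: add level as the only stratum.** Paired simulation, 3,000 trials per scenario. Set (a) keeps each arm's overall curve at Table 9–1. Set (b) applies the Table 9–1 hazard ratios within each level. Level 4 share 50%:

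| Level 5 rate relative to level 4 | (a) without → with level | (b) without → with level |
|---|---|---|
| 1 (not prognostic) | 80.4% → 81.0% | 80.5% → 80.7% |
| 0.67 | 81.6% → 85.3% | 77.2% → 80.7% |
| 0.5 | 81.6% → 90.5% | 68.1% → 79.1% |
| 0.33 | 80.4% → 95.9% | 47.2% → 76.6% |

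At 0.5 with a level 4 share of 25% or 75%, set (a) gives 80.9% → 88.5% and 81.6% → 87.8%; set (b) gives 70.1% → 79.7% and 73.1% → 80.9%. A repeat simulation with 347 evaluable subjects gave 81% → 85%, 82% → 90% and 83% → 97% for (a), and 76% → 80%, 69% → 80% and 48% → 77% for (b). Together the gains are 3 to 4 points at 0.67, 6 to 11 at 0.5 over the three shares, and 14 to 29 at 0.33.

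**Step 3: compare with the planned stratified test.** The number of countries is not stated; 6 countries × 2 vaccination/infection groups are assumed, with the overall curves kept at Table 9–1.
- Level mix equal across countries: 84.6% → 90.8%, 84.3% → 94.1% and 83.5% → 97.5% at 0.67, 0.5 and 0.33. A smaller check at 0.7, 0.5 and 0.35 gave gains of about 4, 8 and 14 points.
- Level 4 share varying from 10% to 90% between countries (1,000 trials): about 84% → 87%, 87% → 92% and 90% → 97% at 0.7, 0.5 and 0.35, gains of about 3, 5 and 8 points before rounding.
- Level not prognostic: 83.5% → 86.8%. This gain of about 3 points is not severity adjustment. Sparse strata give less weight to the late interval, where the hazard ratio is 0.24.

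**Step 4: type I error.** In 4,000 null trials per scenario, one-sided rejection was 2.2% to 2.7% with and without level. The simulation standard error is sqrt(0.025 × 0.975/4000) = 0.25 points, so this agrees with 2.5%.

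**The case against.** Analysing by the randomisation factors is coherent, and nothing in the protocol is miscalculated here. Several points on this side stand:

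- The planned test is already stratified, so a comparison with an unstratified test does not measure the loss from the plan. Country may carry part of the severity information: Section 2.2 says that admission cut-offs for oxygen saturation vary widely between countries. Step 3 is therefore the relevant comparison, and part of its gain is the sparse-strata effect.
- Prognostic strength is assumed. Appendix 2 lets level 4 include care for other medical conditions, and level 2 include home oxygen. Some level 4 subjects may stay long, and a level 5 subject can meet the event by going home on oxygen. Level is a starting point on the scale, not an exact distance to recovery.
- Disease state is a planned subgroup factor, so severity is absent only from the primary analysis.

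A reader might infer that chance imbalance in level biases the result. It does not. With 50% at level 5, the standard deviation of the between-arm difference is sqrt(0.25 × (1/272 + 1/136)) = 5.3 points, so a gap of 10 points or more arises in roughly 6% of trials. It can favour either arm and is already covered by alpha, as Step 4 shows.

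A reader might also infer that the trial misses its 80% target. The documents do not support this. Table 9–1 states overall curves, and with those kept (set a) the unstratified test holds 80% to 82% however prognostic level is. The shortfall in set (b) needs the Table 9–1 hazard ratios to hold within each level, which the protocol does not say.

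**Conclusion.** The point holds as a loss of efficiency. The primary test and the piecewise model omit a baseline measure that is already collected and lies on the scale of the endpoint. The test is valid and alpha is controlled.

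The direction is firm: power is lost whenever level is prognostic, and adding it cost nothing in any scenario tried. The size is conditional on inputs that the protocol does not give. The ranges in Step 2, from 3 to 29 points, are the cleaner measure of what level itself contributes, but their comparator is an unstratified test. Against the planned stratified test the gain is about 3 to 8 points if the level mix differs strongly between countries and 4 to 14 if it is equal. That holds for level 5 rates of 0.7 to 0.35 times the level 4 rate and overall curves as in Table 9–1, and it includes some sparse-strata effect.

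**What to change.** Before unblinding, amend Section 9.4.2 and carry the change into the analysis plan. Stratify the primary log-rank test by the randomisation factors and baseline clinical status (4 or 5, Day 1 pre-dose), and add baseline status as a covariate in the piecewise model. Pre-specify a rule for pooling small countries so that strata stay usable.

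Making level a randomisation factor as well is optional; the analysis change does not depend on it. The cost is about one line of text, with no new data or subjects. The small downside is more strata, which the pooling rule addresses. With 3, 6 or 12 assumed countries the added strata did not reduce simulated power.

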### 9.4.3 Secondary Efficacy Endpoints

Proportion of subjects who are alive and do not require any form of mechanical ventilation at Day 8. Proportion of subjects requiring non-invasive or invasive, mechanical ventilation, proportion of subjects requiring intensive care unit (ICU) transfer, and all-cause mortality rate within 28-day FU period will be presented.

Total duration (days) of oxygen supplementation within 28-day FU period, change from baseline in the nasopharyngeal viral load (RT-qPCR) will be reported as continuous endpoints.

Proportion of subjects with clinical status evolving to each level of the 8-point ordinal scale at Days 2, 3, 4, 8, 15, 22, and Day 29, compared to baseline, will be tabulated in a shift table.

Time to event secondary endpoints will be analysed using a methodology similar to the analysis of the primary efficacy endpoint.

In Part 1, the secondary endpoints will be summarised descriptively.

In Part 2, the comparison between XVR011 and placebo will be conducted for every secondary endpoint and resulting p-values will be presented.

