| 
Primary
 
To evaluate the efficacy of a single intravenous XVR011 infusion in subjects hospitalised for COVID-19, compared to placebo
           | 
 
Time to sustained recovery (i.e., clinical status reaching level 1 to 3 of the 8-point ordinal scale) within 28-day FU period; where recovery must be confirmed to be maintained at level 3 or lower for 14 consecutive days
 
                                                                                                                                                                                                                                                                                                                                                                                                                                                                                                                                                                                                                                                                              |
| 
Secondary
 
To further evaluate the efficacy of a single intravenous XVR011 infusion in subjects hospitalised for COVID-19, compared to placebo
 | 
 
Proportion of subjects who are alive and do not require any form of mechanical ventilation a at Day 8
 
Proportion of subjects requiring any form of mechanical ventilation a within 28-day FU period
 
Proportion of subjects requiring ICU transfer within 28-day FU period
 
Time to sustained hospital discharge (i.e. discharge with no re-hospitalisation after initial discharge for treatment of COVID-19 related events in the following 14 days) within the 90 day FU period
 
Total duration of oxygen supplementation within 28-day FU period
 
Proportion of subjects with clinical status evolving to each level of the 8-point ordinal scale at Days 2, 3, 4, 8, 15, 22 and Day 29, compared to baseline
 
Proportion of subjects with COVID-19 related symptoms
 
All-cause mortality rate within 28-day FU period
 
 |

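### The Part 2 28-day ventilation and ICU-transfer endpoints have no survival condition, so a death without either event counts as a non-event in a between-arm test

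*Protocol*

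**What the plan says.** Table 3–2 (repeated in the synopsis) and Section 9.4.3 of the Protocol list these Part 2 secondary endpoints together:

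- A status at one time point that includes survival: "Proportion of subjects who are alive and do not require any form of mechanical ventilation at Day 8".
- Two cumulative 28-day proportions with no mention of survival: "Proportion of subjects requiring non-invasive or invasive, mechanical ventilation, proportion of subjects requiring intensive care unit (ICU) transfer". Table 3–2 words the second as "Proportion of subjects requiring ICU transfer within 28-day FU period".
- Mortality as an endpoint of its own: "all-cause mortality rate within 28-day FU period will be presented".

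On testing, Section 9.4.3 states: "In Part 2, the comparison between XVR011 and placebo will be conducted for every secondary endpoint and resulting p-values will be presented".

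The only death rule for an efficacy analysis is in Section 9.4.2 and concerns time to sustained recovery: "in case of death events, a censoring time will be imputed to handle deaths similarly to cases of no recovery by Day 29". The same section says that "no mortality or small mortality rate is" anticipated in this population and gives no figure.

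**The concern.** Ventilation and ICU transfer are used here as markers of progression. Death is the worst form of progression: the protocol's own scale (Appendix 2) puts it at level 8, above non-invasive support (6) and invasive ventilation (7). Death also prevents any later ventilation or transfer. A proportion that counts only ventilation or transfer, over all randomised subjects, places a subject who dies on the ward with those who never worsened.

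If such deaths differ between arms, the two comparisons are distorted. An arm with more unventilated deaths looks better on them, and an arm that keeps subjects alive long enough to be ventilated or transferred looks worse. The direction cannot be known in advance. At stake is how far two secondary p-values can support a statement that XVR011 prevents escalation of care.

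**Working it through.** **1. Two records, scored on each endpoint as worded.**

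- *Death on Day 6 on the ward, on low-flow oxygen, never on high-flow oxygen or ventilation, never in ICU.* Day 8 endpoint: failure. 28-day ventilation: non-event. 28-day ICU transfer: non-event. 28-day mortality: event. Primary endpoint: handled like no recovery.
- *The same course with death on Day 12.* Day 8 endpoint: met, because the subject was alive and unventilated on Day 8. Both 28-day proportions: non-event. Mortality: event.

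The Day 8 and 28-day endpoints therefore score the same death in opposite directions only when it occurs by Day 8. For later deaths the non-event scoring remains, without that direct conflict.

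**2. Does another stated rule change this?**

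- Denominator: the Full Analysis Set is primary for all efficacy analyses, and in Part 2 it holds all randomised subjects (Section 9.3). The death stays in.
- Missing data: not imputed unless otherwise stated (Section 9.4.1).
- Death rule: limited to time to recovery (Section 9.4.2). Section 9.4.3 carries similar methodology over to time-to-event secondary endpoints, not to proportions.
- Recorded data: type, flow rate and dates of oxygen support and ventilation (Section 8.1.2). A subject who was never ventilated has no ventilation record.

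None of these moves the subject into either numerator.

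**3. Size.** The plan states no figure to reproduce, and no ventilation, ICU or mortality rate. All rates below are assumptions.

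Affected share = 28-day mortality × share of deaths without ventilation.

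- Low: 0.01 × 0.20 = 0.002, or 0.2 points. That is 0.002 × 136 = 0.3 placebo and 0.002 × 272 = 0.5 XVR011 subjects.
- High: 0.08 × 0.40 = 0.032, or 3.2 points. That is 0.032 × 136 = 4.4 and 0.032 × 272 = 8.7 subjects.
- Relative to an assumed ventilation rate of 10% to 15%: from 0.2/15 = 1.3% to 3.2/10 = 32%. The upper figure takes the worst corner of all three assumptions.

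**4. Effect on the comparison** (placebo vs XVR011; unventilated deaths are added to ventilation to form the composite).

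- Ventilation 12% vs 12%, deaths 3% vs 1%: difference 0 as worded; composite 15% vs 13%, difference −2 points.
- Ventilation 15% vs 13%, deaths 1% vs 3%: −2 points as worded; composite 16% vs 16%, difference 0.
- Ventilation 15% vs 10%, deaths 2% vs 2%: −5 points both ways.
- Ventilation 15% vs 10%, deaths 2% vs 5%: −5 becomes 17% vs 15%, −2 points.
- Ventilation 15% vs 10%, deaths 5% vs 2%: −5 becomes 20% vs 12%, −8 points.

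The last two use a 5% rate of unventilated deaths in one arm, beyond the range in step 3.

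**5. Would a test result change?** For 15% vs 13% with 136 and 272 subjects, SE = √(0.15 × 0.85/136 + 0.13 × 0.87/272) = 0.0368, so z = 0.02/0.0368 = 0.54 and two-sided p is about 0.6. Neither the as-worded 12% vs 12% nor the composite 15% vs 13% would be significant.

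**The case against.** The other side has a good case.

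- *The endpoints answer different questions.* Day 8 is a status at one time; the 28-day proportions are cumulative event counts that match the stated aim of avoiding ventilation and intensive care. A list may hold a composite and its components. This stands. A reader might infer that the protocol contradicts itself, or that it calls such a death a success. It does neither: the favourable scoring follows from the definitions and the denominator.
- *Deaths are visible elsewhere.* 28-day all-cause mortality is in the same sentence of Section 9.4.3 and gets its own comparison; death is level 8 in the shift tables and is treated like non-recovery in the primary analysis. This stands and limits the harm, but it does not correct the two tests.
- *Few subjects are affected.* The Table 3–2 footnote counts high-flow oxygen and CPAP as mechanical ventilation, so a subject must die without either to be missed on the ventilation endpoint. Entry is restricted to levels 4 and 5, and little or no mortality is expected. This stands as a limit on size.
- *Handling of death can be left to the SAP.* Only partly. The difference between the Day 8 and 28-day definitions is fixed in the protocol's objectives table, and an SAP rule adding death would change an endpoint defined there.
- *A composite brings in deaths from other causes and adds mortality to two more tests.* True; it is a cost of the fix.

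**Conclusion.** The point holds as a competing-risk weakness in two Part 2 secondary endpoints. As worded, a subject who dies without ventilation or ICU transfer is a non-event in two between-arm tests, while the Day 8 endpoint treats a death by Day 8 as a failure.

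Its size is uncertain and probably modest: 0.2 to 3.2 percentage points under the assumed rates, and near zero if mortality is as low as anticipated. A reader might go further and infer that the efficacy conclusion is at risk. The documents do not support that: the primary test and sample size do not use these endpoints, mortality is tested separately, and the 15% vs 13% example would not be significant under either definition. It is a cheap improvement worth making, not a flaw that threatens the trial.

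**What to change.** In the synopsis, Table 3–2 and Section 9.4.3, define the tested Part 2 endpoints as the proportion who die or require any form of mechanical ventilation within the 28-day follow-up, and the proportion who die or require ICU transfer within it. This follows the sponsor's own Day 8 construction. Keep ventilation, ICU transfer and death as separately reported components.

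The cost is mainly wording. The composite no longer isolates ventilation or ICU use and includes deaths from other causes; the component results restore that detail.

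One matter must be settled alongside. Section 8.1.1 treats a need for intensive care as treatment failure and calls for the end of study visit, whereas these endpoints and 28-day mortality run over the full 28 days. The two must be reconciled so that ventilation and vital status to Day 29 are captured for these subjects; otherwise neither the present endpoints nor the composites may be fully observed in them.
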